#### Effect modifiers

Single-item measures of gender, socio-economic status (IMD, free school meal status), ethnicity, educational attainment (qualifications being studied and intention to leave school) and religiosity.Self-reported risk behaviours in peer group (four items from existing surveys)School climate and engagement (measured using selected items from the Beyond Blue ‘school climate’ scale, [34]),Parental monitoring. Three new items.Sexual attraction and identity (modified version of the Kinsey Scale; item from Natsal)Self-regulation. Three items drawn from the 36-item Adolescent Self-Regulatory Inventory [35]Importance of social media to social life (two newly designed items)Social network questions, asking about up to six friends (whether or not in the same year group, time spent together online and offline, comfort in sharing something private)Exposure to intervention activities and messages.

#### Outcome data collection

The intervention will be delivered to the S4 student cohort in all six schools between month 20 (August 2017) and month 30 (June 2018), as outlined in the STASH study flow diagram (Fig. 1). All measures will be collected in month 15–18 (March to June 2017) from the previous S4 cohort in each of the six schools who are unexposed to the intervention (since they will have progressed to S5 by the time the intervention is delivered). Collecting data from this previous cohort doubles the information we have to estimate student consent and response rates and evaluate outcome measures, questionnaire content and data collection procedures. It also provides repeated cross-sectional data to assist in the estimation of potential intervention effects. Since both control and intervention students will complete measures in March or June (final month before exams start or first month after exams end), though 1 year apart, their data can be considered comparable.

The baseline/follow-up questionnaire was cognitively tested at stage one via six interviews with students attending the development panels to test comprehension and acceptability of items. Data from the pilot was analysed to check for possible misunderstanding, spread of responses and item-total correlations. The baseline and follow-up questionnaires will be administered as a web-based survey by trained fieldworkers under ‘exam conditions’. ‘Mop up’ visits will be scheduled to collect data from absentees.

### Economic measures and data collection

The aim of the economic evaluation is to assess the feasibility and acceptability of collecting sexual health-related healthcare resource and quality of life (QoL) data to inform the design of a cost-effectiveness analysis to be undertaken alongside a full randomised control trial (RCT). Self-reported health-related healthcare resource use (STI testing and treatment, contraception including out of pocket costs) will be collected via the baseline and follow-up questionnaires and costed using published sources. The CHU9D [36] will be used to calculate quality-adjusted life years (QALYs). In addition, we will undertake a detailed cost analysis of the intervention. This will include time taken in the identification and training of peer supporters and any additional time spent by teachers on the STASH intervention.

### Process measures and data collection

The process evaluation will assess possible mechanisms of impact, feasibility and acceptability of the research design and conduct, implementation and contextual dependence [22]. This involves examination of acceptability of intervention form and content; reach; exposure; fidelity (the extent to which the intervention delivered as intended); contextual factors including barriers to, and facilitators of, implementation; factors affecting recruitment and retention; relevance to the target group; and perceived impact of the intervention. The process evaluation will contribute to developing the STASH programme theory by exploring whether and how norm change and social support for healthy sexual behaviour is spread through a relatively closed social system, identifying which components are potentially most important to the intervention’s success and providing possible explanations for components that did not work so well.

Feasibility study process evaluation work will involve basic evaluation activities in all six schools and in-depth evaluation activities in two to four ‘case study’ schools. Case study schools will be selected on the basis of school location/population served (urban/semi-urban), school size and proportion of free school meals.

Basic evaluation activities will comprise the following: (1) quantitative student evaluation of two-day peer supporter training; (2) interviews with all three trainers; (3) online questionnaire to be completed by all trained peer supporters focusing on reasons for engagement/non-engagement, preferred communication approaches, perceived challenges and factors facilitating role, perceived response of peers; (4) social network analysis (data from baseline and follow-up questionnaire and Facebook group membership); (5) project monitoring log capturing information including percentage and characteristics of those completing training/accepting role/formally withdrawing, field notes on relevant meetings and relevant contemporaneous events; (6) peer supporter activity log (on group membership, posting activity, face-to-face conversations); (7) analysis of relevant items from the follow-up questionnaire on exposure and effect modifiers; (8) fieldwork/trainer observation pro formas for individual intervention delivery and data collection sessions.

In-depth evaluation activities will include the above with the addition of (9) structured observation of peer supporter training to assess engagement by peer supporters and document reactions to the intervention, (10) friendship group interviews with trained peer supporters (one to two groups per school), (11) paired/group interviews with non-peer supporter S4 s (one to two groups per school) and (12) individual interviews with teachers (two per school).

### Data analysis

#### Evaluation feasibility and acceptability outcomes

The feasibility and acceptability outcomes that constitute the progression criteria (Table 1) will be summarised overall and (anonymously) by the school.

The data linkage acceptability question will be summarised overall and by key factors at baseline (such as socio-demographic, sexual experience).

#### Baseline characteristics

Baseline characteristics (including deprivation) will be summarised overall and by study group (intervention/control) and for those who were and were not followed up (or dropped out of intervention). Exploratory investigations of the associations between baseline characteristics and successful follow-up may be carried out using appropriate statistical tests and mixed effects logistic regression models (to reflect the clustered nature of the data by school), to identify potential sources of bias in future studies.

#### Outcome data

Outcome data will be summarised overall and by study group. Mixed-effects regression models, with a random effect for school, will be used to estimate the magnitude of intervention effects with 95% confidence intervals. The effects of individual-level factors (effect modifiers) potentially associated with outcomes will be explored by extending these regression models, to identify key trial design parameters in future studies. Interaction models may be considered to explore whether the intervention might be more or less effective (or inferior) for particular subgroups of students. The within-school intra-class correlation coefficients will be reported for each outcome and used to inform sample size calculations for the future RCT. The study is powered for exploratory analysis only and so analyses will not be testing hypotheses regarding intervention effectiveness. Missing data will not be imputed since this is a feasibility study.

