**Methods/design:**

This protocol describes a feasibility trial of the STASH intervention in six schools. It builds on an earlier study phase of intervention co-development using patient and public involvement (PPI) activities, followed by a pilot of intervention components and evaluation tools in one school. Participants are fourth year (S4) students (aged 14–16) in state-funded Scottish secondary schools who have received some level of teacher-led sex education. The previous cohort of S4 students (those completing S4 in the year prior to the intervention) will serve as controls. Data will be collected from controls (month 16), baseline (month 20–21) and follow-up (month 27–30) via a web-based questionnaire, which will measure (and test the reliability of) primary outcome measures for a phase III trial (delayed initiation of/abstinence from sex and consistent condom use), secondary outcomes and mediators of sexual behaviour (including school climate and social networks). The main feasibility outcome is whether the study meets pre-set progression criteria regarding feasibility and acceptability, measured largely via a process evaluation (basic measures in all 6 schools and in-depth in 2-4 schools). An economic evaluation reporting costs alongside consequences will be conducted.

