The feasibility of recruitment of schools to cluster randomised trials has been well established in many previous trials, so we have opted to implement the intervention in all six study schools, rather than recruit a larger number of schools and randomise half to the control. The prior cohort of S4 students (i.e. those completing S4 in the year prior to the intervention) in each school will complete the outcome questionnaire towards the end of their academic year (and prior to implementation of the intervention in the subsequent cohort of S4 students) and their data will be compared with the cohort of S4 students participating in the intervention. Therefore, the prior cohort of S4 students will serve as controls who received usual provision of sex and relationships education, which in most Lothian schools is a version of the Sexual Health And Relationships Education (SHARE) package [24].

Schools will be considered formally recruited to the study on the administration of the control questionnaire and signature of the research contract by a senior staff member. Any school opting to discontinue with the study after this point will be considered a withdrawal.

To maximise retention, schools will be given £500 to compensate for disruption to school life due to the questionnaire and process evaluation activities, plus £500 to compensate for staff time taken up by intervention activities (e.g. staff attendance at training).

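### The cohort coefficient estimates STASH plus any change between the 2017 and 2018 S4 years, so it should not be labelled an intervention effect or rest on the two cohorts being comparable

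*Protocol article*

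**What the plan says.** Sample size and selection explains the allocation: "we have opted to implement the intervention in all six study schools, rather than recruit a larger number of schools and randomise half to the" [untreated arm]. It also defines the comparison group: "the prior cohort of S4 students will serve as controls who received usual provision of sex and relationships education".

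Outcome data collection gives the control survey date: "All measures will be collected in month 15–18 (March to June 2017) from the previous S4 cohort in each of the six schools". The abstract lists the waves: "Data will be collected from controls (month 16), baseline (month 20–21) and follow-up (month 27–30". Since month 20 is August 2017 and month 30 is June 2018, follow-up runs from March to June 2018.

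Outcome data collection argues that, because both cohorts answer in March or June, "though 1 year apart, their data can be considered comparable". It gives this use for the control data: "It also provides repeated cross-sectional data to assist in the estimation of potential intervention effects".

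Outcome data, under Data analysis, then specifies the estimate: "Mixed-effects regression models, with a random effect for school, will be used to estimate the magnitude of intervention effects with 95% confidence intervals". Extensions of the model with individual-level factors are described as exploratory.

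**The concern.** The control and intervention cohorts differ in two ways at once: exposure to STASH, and the year in which they were in S4. Intake, the teacher-led sex education received, local services and social media habits can all change between consecutive years. The protocol names no calendar-year term, earlier control year, concurrent untreated school or external trend series that would isolate STASH from such change.

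The comparability argument rests on the month of the survey. Matching the month deals with season and closeness to exams. It does not deal with the year.

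What is at stake is the meaning of the reported number. A shared one-year drift could look like benefit, or could mask it, and a confidence interval labelled as belonging to an intervention effect would give the reader no warning.

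**Working it through.** **Inputs from the protocol.** Six schools, all receiving STASH; one control cohort per school (2017) and one intervention cohort per school (2018); about 700 students per cohort, or 700/6 ≈ 117 per school, so 6 × 117 = 702; ICC of 0.01 or 0.03 (Sample size and selection, where these values are given for a future trial). The protocol states no figure for the cohort contrast, so there is none to reproduce.

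**Step 1: can STASH and year be separated?** Write the model as outcome = school + b × STASH + c × year + error. Across the 12 school-by-cohort cells, STASH = 0 exactly when year = 2017, and STASH = 1 exactly when year = 2018. With six school columns plus STASH and year, the design matrix has 8 columns and rank 7. Only b + c can be estimated. A random effect for school removes stable differences between schools; it does not break this identity.

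**Step 2: does the baseline wave help?** Only the intervention cohort has one. There are three wave means (control at end of S4, intervention at start of S4, intervention at end of S4) and four unknowns (intercept, cohort/year, ageing within S4, STASH). The rank is 3 of 4, so STASH is still not identified.

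**Step 3: size, under assumed drifts.** Take a true STASH effect of zero. In SD units, the standard error of the within-school cohort contrast is

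SE = sqrt(2 × (1 − ICC) / 702)

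- ICC 0.01: sqrt(1.98/702) = 0.0531
- ICC 0.03: sqrt(1.94/702) = 0.0526

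The chance that the 95% interval excludes zero is P(Z > 1.96 − d/SE) + P(Z < −1.96 − d/SE), where d is the drift.

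For a binary outcome at an assumed 25%, SD = sqrt(0.25 × 0.75) = 0.433. The SE is then 0.433 × 0.0531 = 0.0230, or 0.433 × 0.0526 = 0.0228.

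| Assumed drift | d/SE (ICC 0.01 / 0.03) | Interval excludes zero |
|---|---|---|
| None | 0 | 5% |
| 0.05 SD | 0.94 / 0.95 | 15.6% / 15.8% |
| 2 points at 25% | 0.87 / 0.88 | 14.0% / 14.2% |
| 5 points at 25% | 2.17 / 2.20 | 58% / 59% |

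**Step 4: check by simulation.** With 20,000 runs per scenario, 117 students per school per cohort, an assumed prevalence of 30% and an assumed ICC of 0.02, the mean estimate equalled the drift: 0.02 for 2 points and 0.05 for 5 points. The interval contained zero in 86% and 47% of runs, so it excluded zero in 14% and 53%. This agrees with the formula after allowing for the higher prevalence.

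**The case against.** The prior-cohort design is disclosed and justified, and the protocol describes the study as non-randomised. Sample size and selection says the study is not designed to identify an effect estimate. Outcome data calls the analysis exploratory and says it will not test effectiveness hypotheses. The drifts above are assumed, and they are expressed through exclusion of zero, which the protocol does not propose to use as a test. Individual-level factors are already foreseen as model extensions.

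Much of this stands. The problem comes from the design rather than from a poor choice of model, and measured shifts in intake can be partly adjusted for. The caveats do not settle the point, though. They concern power and testing, not what the coefficient measures, and none of them mentions year-to-year change. The comparability statement asserts the opposite.

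A reader might infer more than the protocol supports:

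- **That the progression decision is compromised.** The four criteria in Table 1 cover recruitment and training, peer-supporter activity, acceptability and response rates. None uses an outcome effect.
- **That the estimate will set the phase III effect size.** The objectives list recruitment and retention, outcome measures, intra-cluster correlation and sample size as design parameters; effect size is not named. In Outcome data, it is the intra-class correlations that feed the sample size calculation.
- **That the drifts can be scaled against the 0.1 effect size in Sample size and selection.** That figure relates to a future trial and has no stated scale.
- **That items STASH should not move could measure the drift.** Parental monitoring might be affected by STASH, and such items need not drift as sexual behaviour does.

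**Conclusion.** The point holds as a matter of labelling and interpretation. Study group and survey year are the same variable in all six schools, so the coefficient is the 2018 minus 2017 cohort difference. Calling it an intervention effect, and calling the data comparable because the survey months match, are both wrong as written. This conclusion needs no assumption about the size of drift.

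The illustrative rates of about 16% (0.05 SD), 14% (2 points) and 59% (5 points), against a nominal 5%, do depend on the assumed drifts and on the 25% prevalence. They show what such drifts would do, not what is expected. The consequence is limited to how the exploratory outcome results are read.

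**What to change.** 1. In Outcome data, call the estimate the difference between the 2018 and 2017 S4 cohorts, and state that it comprises STASH plus any year-to-year change and that its interval covers sampling error only.
2. In Outcome data collection, limit the comparability statement to time of school year.
3. Make the main cohort contrast an adjusted one, using characteristics that STASH cannot change and that are collected in both cohorts: gender, deprivation, free school meal status and ethnicity. State that this handles measured shifts in intake only, not changes in teaching, services or norms.

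The cost is small: two wording changes and one adjusted model on data already planned for collection. As missing data will not be imputed, students lacking a covariate would drop out of the adjusted model, so its number analysed should be reported. The claim becomes weaker, but it is one the study says it was not designed to make.

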### Sample size and selection

As a feasibility study, STASH is not designed to identify an estimate of effect and thus a standard power calculation is not appropriate. Allowing for non-response of 15% due to student absence, the sample size across all six schools is approximately 700 intervention participants and 700 controls. This should be sufficient to allow qualitative and quantitative progression criteria to be assessed and provide information on key parameters for the design of a future trial. It is premature to specify the required sample size for a future trial but is nevertheless useful to have a broad indication of the likely size of such a trial. It is anticipated that a full trial would be cluster randomised, with school as the unit of randomisation. Assuming a mean school year size of 150 students and an effect size of 0.1, then a trial of between 15 and 25 schools per arm would have 80% power across a range of scenarios in which (1) intra-cluster correlation is assumed to be either 0.01 or 0.03, (2) there is one or two primary outcomes, and (3) follow-up rates vary between 75% and 85%.

Schools will be recruited via local authority education services. STASH project staff will initially contact school management teams by email and meetings will be arranged with those expressing interest. Follow-up emails and calls will be made as necessary. Response rates, and any stated reasons for non-participation, will be recorded. Schools will be recruited on a first come, first served basis, while keeping mindful of the need to ensure variation in terms of school size, geographic location and area deprivation.

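### The effect model names a random effect for school only, but exposure changes by school-year, so unless school effects are perfectly stable from year to year the 95% intervals are too narrow

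*Protocol article*

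**What the plan says.** Under Sample size and selection, the protocol article explains that school recruitment to cluster trials is already known to be feasible, "so we have opted to implement the intervention in all six study schools". The comparison group is historical and within school: "the prior cohort of S4 students will serve as controls who received usual provision of sex and relationships education". The planned numbers are given as follows: "the sample size across all six schools is approximately 700 intervention participants and 700 controls". Outcome data collection adds, of the control cohort's data: "It also provides repeated cross-sectional data to assist in the estimation of potential intervention effects".

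Under Data analysis, Outcome data, the effect model is "Mixed-effects regression models, with a random effect for school, will be used to estimate the magnitude of intervention effects with 95% confidence intervals". On the intra-class correlation, the same paragraph says: "The within-school intra-class correlation coefficients will be reported for each outcome and used to inform sample size calculations for the future RCT". The trial that this ICC is meant to serve is described under Sample size and selection: "It is anticipated that a full trial would be cluster randomised, with school as the unit of randomisation". It is planned on a mean school year of 150 students, with ICCs of 0.01 or 0.03.

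The article limits the weight of the effect analysis. It says that "STASH is not designed to identify an estimate of effect", and Outcome data describes the analysis as exploratory, with no test of effectiveness.

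**The concern.** Each school contributes one unexposed year group and one exposed year group. Exposure is therefore constant within a school-year and changes only between a school's two years: 12 school-years and six within-school contrasts.

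A random effect for school absorbs what the two year groups of a school have in common. With balanced data that part drops out of the cohort difference altogether. What remains is student-level noise plus any variation between schools in how their S4 year groups change from one year to the next. The stated model has no term for the second part and treats students as independent conditional on school. A prior-cohort control is exposed to exactly this variation.

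Two outputs are affected. The first is the confidence interval for the effect, which is the only inferential statement left once testing has been ruled out. The second, depending on how it is estimated, is the ICC carried forward to the full trial.

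**Working it through.** **Inputs from the protocol article.** Six schools and two cohorts; about 700 students per cohort, so m = 700/6 ≈ 117 per school-year; ICC 0.01 or 0.03 (Sample size and selection).

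**Assumption.** The year-to-year correlation of school effects, r, is not given. I take r = 1, 0.9, 0.8 and 0.5.

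**The plan's own figures.** The article gives no coverage or standard error to reproduce. Its 15 to 25 schools per arm for the full trial cannot be re-derived, because the scale of the effect size of 0.1 and the control rate are not given. That figure is not used below.

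**Variance components, total variance 1.** School variance shared by both years = ICC × r. School-by-year variance s²c = ICC × (1 − r). Student variance s²e = 1 − ICC.

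**Variance of the cohort difference.**
- True: 2(s²c + s²e/m)/6
- Reported by the school-only model: about 2(s²e/m)/6
- Ratio of true to reported SE: √(1 + s²c/(s²e/m))
- Coverage of a nominal 95% interval: 2Φ(1.96/ratio) − 1

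Worked case, ICC 0.03 and r = 0.8: s²c = 0.03 × 0.2 = 0.006; s²e/m = 0.97/117 = 0.00829; ratio = √(1 + 0.006/0.00829) = √1.724 = 1.31; coverage = 2Φ(1.49) − 1 ≈ 86.5%.

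| ICC | r | s²c | SE ratio | Coverage |
|---|---|---|---|---|
| 0.01 | 1 | 0 | 1.00 | 95.0% |
| 0.01 | 0.9 | 0.001 | 1.06 | 93.6% |
| 0.01 | 0.8 | 0.002 | 1.11 | 92.2% |
| 0.01 | 0.5 | 0.005 | 1.26 | 88.0% |
| 0.03 | 1 | 0 | 1.00 | 95.0% |
| 0.03 | 0.9 | 0.003 | 1.17 | 90.7% |
| 0.03 | 0.8 | 0.006 | 1.31 | 86.5% |
| 0.03 | 0.5 | 0.015 | 1.68 | 75.8% |

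Simulation of balanced Gaussian data (6 schools × 2 cohorts × 117) agrees to within about 0.2 percentage points. In the same simulations a paired t interval on the six within-school differences (5 df) covers 95% throughout.

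**In percentage points.** For a proportion near 50%, ICC 0.03 and r = 0.8, the reported half-width is 50 × 1.96 × √(2 × 0.00829/6) ≈ 5.2 points. With the true SE it is 50 × 1.96 × √(2 × 0.01429/6) ≈ 6.8. With t on 5 df (2.571 in place of 1.96) it is about 8.9.

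**Outcomes among sexually active students.** The article gives no proportion sexually active. Assuming about 39 per school-year (a third of 117), the student-level noise is larger and the SE ratio is only about 1.02 to 1.27 over the same ICCs and r = 0.9 to 0.5.

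**ICC.** A single-year parallel trial needs the shared school variance plus s²c. A pooled school-only model estimates the shared variance plus s²c/2, so its expected ICC is about ICC × (1 + r)/2. That is a factor of 0.95, 0.90 or 0.75 at r = 0.9, 0.8 or 0.5. A true 0.03 becomes 0.0285, 0.027 or 0.0225; a true 0.01 becomes 0.0095, 0.009 or 0.0075. With six schools, the simulated 95% range of the estimate at true ICC 0.03 and r = 0.8 is about 0.001 to 0.07, far wider than the bias.

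**The case against.** The strongest reply is that nothing in the study is decided by these intervals. All four progression criteria in Table 1 concern recruitment and training, role completion, acceptability and response rates; none uses an effect estimate or an ICC. The article disclaims effect estimation and effectiveness testing. This stands, and it lowers the severity. It does not make the interval correct: a reported 95% interval claims 95% coverage, whether or not a test accompanies it.

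Second, the loss depends on a correlation the document does not supply. That also stands. At r = 1 the stated model is sound, and at ICC 0.01 with r = 0.9 the shortfall is about one percentage point.

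Third, an article may leave model detail to a statistical analysis plan. Degrees of freedom and the ICC estimator could well be settled there. The random-effect structure, however, is stated here, and as stated it does not match the level at which exposure varies.

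Three stronger readings are tempting but unsupported:
- A reader might infer that the full trial will be undersized. The article does not say the ICC comes from the pooled two-cohort model, and a within-cohort ICC would fit its wording. It says the ICC will inform the sample size, not determine it alone. A six-school estimate can also fall on either side of the truth.
- A reader might convert the ICC's uncertainty into a range of schools per arm. That needs the scale of the 0.1 effect size, which is not given.
- A reader might say that the model takes some 1,400 students as fully independent. It takes them as independent conditional on school.

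**Conclusion.** The concern holds in a conditional form. The stated random effect sits at school level while exposure varies at school-year level, so any school-by-year variance makes the reported intervals too narrow. Over assumed correlations of 0.9 to 0.5 and 117 students per school-year, coverage is about 94% to 88% at ICC 0.01 and 91% to 76% at ICC 0.03. The loss is smaller for outcomes among sexually active students.

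The ICC half is weaker. It applies only if the ICC is taken from the same pooled model, and an average bias of 5% to 25% is smaller than the sampling error from six schools.

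The calculations use Gaussian variance components and equal school sizes. The severity is moderate: the consequence is overstated precision in exploratory effect estimates and possibly a somewhat low ICC, not a wrong progression decision.

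**What to change.** In Outcome data, add a school-by-cohort random effect to the effect model, or analyse the six within-school cohort differences. Use t intervals on 5 df in either case, because a variance component resting on six schools is poorly estimated and may come out at zero.

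Describe the result as a between-cohort difference. No random effect can separate the intervention from a one-year change common to all six schools.

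State that the ICC is estimated within cohort and report it with its 95% CI, so that the design of the full trial can take account of its imprecision.

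This needs a sentence or two of wording and no new data. The price is wider intervals: even with no school-by-year variance, moving from 1.96 to 2.571 widens them by 2.571/1.96 = 1.31, about 31%.
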